##### Safety analyses

2.7.3.2

AEs will be analyzed using the Common Terminology Criteria for Adverse Events (version 5.0) according to the Medical Dictionary for regulatory activities (79). The frequency and percentage of participants experiencing each specific AE will be tabulated by severity and treatment. Each AE will be counted once under the maximum severity or the strongest recorded causal relationship to the studied product. For each arm, all AEs will be grouped by organ class and, for each AE, the relative risk and absolute risks between arms with their 95% confidence intervals will be calculated.

#### Oversight and monitoring

2.7.4

An independent data and safety monitoring board will review the accumulated data to assure that the safety of study participants is protected while the scientific goals of the study are being met. The data and safety monitoring board is responsible for conducting reviews of accumulating safety and efficacy data once a year. It may recommend halting or modifying study procedures if there is a clear and evident reason related to the safety of the study participants including and excess in frequency of any AE (judged by the data and safety monitoring board to be harmful to the participants) in one of the arms, and an excess in frequency of any SAE (grade 3 and higher) in one of the arms.

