### Study design

2.2

CANSEP is a double-blinded, randomized, factorial, placebo-controlled trial in a cohort of PwMS with an incomplete response to standard treatments, using various measurements, and thorough, multidisciplinary outcomes. Up to 4 visits are scheduled during this trial. Visit 1 is dedicated to the consent process and the confirmation of eligibility criteria. Outcomes assessments are done during visit 2 (baseline) and during visit 3 which takes place after 4 weeks of treatment. Finally, outcomes assessments are also carried out during a fourth visit which is scheduled 12 weeks after the end of the initial treatment period for responders only, i.e., patients who have a decrease in mean Numeric Rating Scale (NRS) of at least one point compared to baseline. Indeed, spasticity will be assessed using the NRS (22), but the spasticity outcome analyzed in this trial will be the mean NRS score over 7 days (mNRS). Blood samples will be collected to measure immunological and neurobiological markers in order to investigate the underlying physiological responses of each treatment administration, and to identify potential mechanisms of their therapeutic effects. The study plan is represented in Figure 1.

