
### Randomization

2.4

Patients who meet all the inclusion criteria and none of the exclusion criteria and consent to take part in the trial after they have received the study oral and written information, will then be randomly assigned in equal proportions to either THC, CBD, THC + CBD, or placebo using stratified block randomization. Randomization will be stratified by sex and baseline mean spasticity score. In each of the 4 strata, corresponding to different combinations of sex (male vs. female) and baseline mean spasticity score ([2-6[vs. ≥6), randomization will be performed using blocks of size 4. This will minimize the imbalance between group sizes, while preventing unblinding of the treatment allocation of consecutive participants. The randomization schedule will be generated by CHUM’s Centre for the Integration and Analysis of Medical Data (CITADEL), who will send the randomization codes to the CHUM research pharmacy and keep secure digitalized copies. Randomization codes will be maintained throughout the study.

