#### Sample size and power calculation

2.7.1

The sample size for this trial was calculated using ‘pwr.t.test’ (for a Student t-test) in the ‘pwr’ package in R statistical software (70). The required sample size was estimated to ensure at least 80% power, with a two-sided alpha significance level of 5%, to detect clinically important effects of the two factors THC and CBD, on spasticity, which is the primary outcome (71). A target total recruitment of 200 patients would cover scenarios with a mean change from baseline among treated patients ranging from −1.90 to 1.55, where −1.55 is what we consider to be the minimal clinically significant effect (22, 33, 72, 73). However, some power would be lost upon Bonferroni adjustment. Thus, a target total recruitment of 250 patients would be more adequate, after accounting for a potential rate of attrition of 5% over the study period, based on previous studies (22, 33, 72, 73) and the clinical experience at the CHUM MS Clinic.

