#### Primary endpoints

2.7.2

Firstly, an analysis of variance (ANOVA) will be used to assess the treatments effect on the differences in the mNRS from baseline to week 4. The normality of the responses will be assessed using normal-quantile plots. The ANOVA model will only include the factors THC and CBD. Secondly, an analysis of covariance (ANCOVA) will be used to evaluate the treatments effect on the post-intervention mNRS while adjusting for baseline mNRS and sex (stratification variables). The ANCOVA may reduce potential bias present in the ANOVA model (74). Finally, the ANCOVA model described above will be expanded by including potential confounders, such as biomarkers, for which a clinically meaningful difference between any two groups will be revealed by the preliminary descriptive analysis. The estimated adjusted and unadjusted differences in mNRS from baseline to week 4 and their 95% confidence intervals will be reported for all models.

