#### Sensitivity analysis

2.7.6

To test if our conclusions are robust to the invalidity of the hypothesis of no interaction between the factors, we will use an ANOVA model including THC, CBD, and their interaction. We expect to find a negligible interaction effect.

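### Adverse-event comparisons and the board's example grounds are worded by arm only; adding the THC and CBD margins would use the factorial design and sharpen each cannabinoid's safety estimate

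*Protocol article*

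**What the plan says.** **Design.** Study design (2.2): "CANSEP is a double-blinded, randomized, factorial, placebo-controlled trial in a cohort of PwMS with an incomplete response to standard treatments". Randomization (2.4): patients are "randomly assigned in equal proportions to either THC, CBD, THC + CBD, or placebo using stratified block randomization".

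**Efficacy works on the factors.** The sample size (2.7.1) is set "to detect clinically important effects of the two factors THC and CBD, on spasticity". For the primary endpoint (2.7.2), "The ANOVA model will only include the factors THC and CBD". On the product term, Sensitivity analysis (2.7.6) says: "We expect to find a negligible interaction effect".

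**Safety works on the arms.** Under Safety analyses (2.7.3.2), events are tabulated by severity and treatment, and for each event "the relative risk and absolute risks between arms with their 95% confidence intervals will be calculated". Under Oversight and monitoring (2.7.4), the board meets yearly and may recommend halting or changing study procedures for a clear safety reason. Two examples follow: an excess of any adverse event "judged by the data and safety monitoring board to be harmful to the participants) in one of the arms", and an excess of any serious adverse event, again in a single arm. No comparator or threshold is given. The word that introduces the examples makes the list open.

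**Aim.** The second main aim (1.2) is the tolerability of THC and CBD, each alone and combined.

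**The concern.** If THC causes an adverse event and CBD does not modify that effect, the event rises in two arms together: THC alone and THC/CBD. A harm of CBD likewise rises in CBD alone and THC/CBD. The most informative comparison for a single cannabinoid's harm is then half the trial against the other half, which is how efficacy is handled. The safety sections name only arm-level comparisons, so each cannabinoid's harm would be estimated from two of the four arms at a time.

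At stake is the precision of the answer to a stated main aim. A smaller matter is whether the board's tables bring a shared excess to its attention. The examples in 2.7.4 describe one arm standing out and do not mention an excess shared by two arms.

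**Working it through.** The documents give no adverse-event rates and no safety power figure, so there is no plan figure to reproduce. The rates below are assumptions.

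**Inputs from the protocol.** Target 250 in four equal arms: 250/4 = 62.5, taken as 62 per arm and 124 per margin. Accrual: 41 randomized between 10 November 2022 and 29 May 2024 (566 days), about 10 per arm. The pace is 41 × 365.25/566 = 26.5 a year, or 6.6 per arm a year.

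**Size of the effect seen.** Let p0 be the event risk without THC and p1 the risk with THC, with no interaction. Take p0 = 10% and p1 = 25%.

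- THC versus placebo: 25 − 10 = 15 points, the full effect.
- THC-containing versus THC-free: 25 − 10 = 15 points, the full effect.
- One THC arm versus the other three pooled: the comparator is (10 + 10 + 25)/3 = 15%, so the difference is 10 points, one third less. The protocol does not specify this comparison.

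**Precision.** With n per side, SE = √[(p0(1−p0) + p1(1−p1))/n].

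- THC versus placebo: √[(0.09 + 0.1875)/62] = 0.0669; 95% half-width 1.96 × 0.0669 = 13.1 points.
- THC margin: √[(0.09 + 0.1875)/124] = 0.0473; half-width 9.3 points.
- Ratio: √2 = 1.41, whatever the rates.

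**Power.** Exact enumeration of the two-sided 5% Fisher test, used only as a yardstick because the protocol plans estimates with confidence intervals:

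| Per arm | Assumed rates | One THC arm v other three | THC v placebo | THC margin |
|---|---|---|---|---|
| 62 | 2% v 8% | 22% | 16% | 47% |
| 62 | 10% v 25% | 39% | 51% | 85% |
| 62 | 5% v 20% | 47% | 65% | 94% |
| 25 | 10% v 25% | 17% | 18% | 41% |
| 10 | 10% v 25% | 8% | 3% | 14% |

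**Reading several arm contrasts.** A simulation with a pooled z-test at 1.96 (62 per arm, 40,000 runs) gives the chance that at least one contrast is significant in the direction of harm:

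| Assumed rates | Either THC arm v placebo | Any of four THC v non-THC pairs | THC margin |
|---|---|---|---|
| 5% v 15% | 64% | 81% | 77% |
| 10% v 25% | 76% | 90% | 89% |
| 20% v 40% | 83% | 94% | 93% |

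Scanning all four pairs matches the margin's chance of a signal, but by taking four uncorrected looks per event. Each of those estimates keeps the wider interval.

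**What the margin hides.** If a harm occurs only with the combination and adds d points there, each margin shows d/2. An excess of 15 points would appear as 7.5, so the four-arm comparison must stay.

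**The case against.** A reader might infer that a harm of THC or CBD is diluted under this plan and likely to be missed, or that the board cannot act on an excess seen in two arms. The documents do not support this.

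- **The board's list is open.** The two single-arm cases are examples, the power is permissive, and it rests on judgement. Members who see four arms side by side could notice the same event raised in two of them.
- **Dilution needs a comparator that the text does not give.** It arises only if one arm is set against the other three pooled. Section 2.7.3.2 plans contrasts between arms, which cover THC versus placebo and CBD versus placebo, where a component harm appears at full size.
- **Missing the harm is not the general case.** With 10% v 25% at full enrolment, at least one THC arm is significant against placebo in 76% of runs. For rarer events (2% v 8%) a single pair is weak at 16%, but the margin reaches only 47%.
- **Early reviews gain little.** At about 10 per arm every contrast is weak (3% and 14% above). The board also reviews accumulated data, so the yearly increment of 6 to 7 per arm understates what it sees.
- **Arm-level safety answers a stated aim**, and the negligible interaction in 2.7.6 is expected for the spasticity model, not for adverse events.
- **Some safety outcomes may already be analysed by factor.** Section 2.7.3 sends secondary outcomes to the spasticity methods, and the abstract counts adverse events among them. That plausibly covers scales such as psychotic symptoms and cognition. For adverse events, the more specific text in 2.7.3.2 names only arm contrasts.
- **Detail may sit in a board charter or analysis plan** not shown here.

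These arguments remove any claim that the plan is wrong. They leave a narrower point: for adverse events the article states its comparison, and a more precise one is available from the same data.

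**Conclusion.** The point holds as a cheap improvement. Both safety sections are worded by arm only, while efficacy is powered and analysed on the factors. Adding the margins cuts the standard error for each cannabinoid's harm by a factor of 1.41. In the middle scenario (10% v 25%, 62 per arm), the half-width falls from about 13 to 9 points and power rises from 51% to 85%.

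The 1.41 ratio depends only on equal allocation and little interaction. The power figures also depend on the assumed event rates and on the Fisher test as yardstick. Nothing here shows that the board is prevented from acting, or that the planned contrasts are biased.

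**What to change.** **In 2.7.3.2**, keep the four-arm comparisons and add, for each adverse event, the risk difference and relative risk with 95% confidence intervals for THC-containing versus THC-free arms and for CBD-containing versus CBD-free arms. Restrict these to the common 4-week period, because only responders enter the extension and later exposure is no longer a comparison of all randomized patients. The four-arm table still serves the aim on tolerability alone and in combination, and keeps a harm specific to the combination visible.

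**In 2.7.4**, give the board the same two margins beside the four arms, and state that an excess shared by two arms falls within its open list of grounds. Set no threshold; the judgement stays with the board.

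**Cost.** A sentence in each section and extra columns in the board and final safety tables, with no new data or patients. The downside is more comparisons to interpret, and margins that can mislead if the two cannabinoids interact on an adverse event. They should therefore always be read with the four arms.

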#### Missing data and dropouts

2.7.5

Missing data could occur due to two types of reasons: a missing or illegible item response and a missed visit. We will report the percentage of missing values for each variable of interest by visit. Missing values for the primary outcome at follow-up will be imputed by the baseline value resulting in null change from baseline. No imputation for the primary outcome will be needed from the per-protocol analysis. For the ANCOVA models, imputation of missing covariate values will be handled by multiple imputation methods using chained equations. Since we cannot verify the missing at random hypothesis, which is required for the valid use of this imputation method, we will perform a sensitivity analysis with complete cases only.

#### Sensitivity analysis

2.7.6

To test if our conclusions are robust to the invalidity of the hypothesis of no interaction between the factors, we will use an ANOVA model including THC, CBD, and their interaction. We expect to find a negligible interaction effect.

## Discussion

3

Current therapeutic approaches for MS have partial efficacy. Disease-modifying therapies are limited in their action on MS symptoms (11). Both preclinical and clinical data support that analgesic, antihyperalgesic, neuroprotective, and anti-inflammatory properties have been attributed to cannabis-derived cannabinoids, essentially THC and/or CBD (30, 80). The CANSEP trial is part of a large Canadian Institutes of Health Research program on cannabis research in priority areas (21). It was developed in response to the lack of evidence about the safety and the efficacy of specific cannabinoids in MS (20). The originality of our study comes from the fact that we will compare the distinct and combined effects of THC and CBD on spasticity and other symptoms such as pain, sleep, well-being, and quality of life of Canadian PwMS.

CANSEP will fill a knowledge gap since no Canadian study has yet systematically compared the two main cannabinoids, THC and CBD, and their combination, to placebo, as an add-on treatment for spasticity. This will answer the urgent need to assess cannabinoids’ efficacy on spasticity and other symptoms in MS in addition to their acceptability and safety when used as an add-on therapy to usual standard treatments. Additionally, CANSEP can provide explanations for potential therapeutic mechanisms and/or AEs such as gastrointestinal and psychiatric/cognitive effects associated with each type of cannabis-based medication in PwMS that are still poorly understood (18). For example, the polymorphism in cannabinoid receptor 2 associated with reduced endocannabinoid effects is more prevalent in autoimmune diseases, including MS (81). Thus, CANSEP will provide a better characterization of CBD and THC influence on immune and pharmacological factors which could directly influence spasticity to guide both health professionals and PwMS in the decision-making process. Indeed, while our main concern is spasticity, we are also evaluating other MS symptoms (pain, fatigue, bladder, bowel, and sexual dysfunctions, mobility, the restless legs syndrome, mental health, cognition, and quality of life). The CANSEP trial’s results will impact how these different symptoms could be managed and will provide a better grasp of tolerance and toxicity. We have a long experience with MS patients, and the trial’s results will provide guidance to a better control of symptomatic aspects of MS with cannabinoids. It will also guide health professionals and PwMS on the treatment’s dose and frequency.

Another strength of this trial is the development of two ancillary studies. Participants are free to take part or not in these ancillary studies without affecting their participation in the CANSEP clinical trial.

Ancillary study 1 – Perception of Canadian patients with MS on the use of cannabis for a better management of the disease symptoms (PerSPective Study): The main objective is to conduct a pan-Canadian online survey, co-created for and with PwMS to identify facilitating or limiting factors on the use of medical cannabis by PwMS to anticipate the strategies to be put in place depending on the results of the research.Ancillary study 2 – Patient experience assessment of participants in the CANSEP trial and the contribution of patient partner researchers in the implementation work of this project (EXPECT Study): This study includes quantitative questionnaires and semi-structured qualitative interviews to understand how the patient partners involved in CANSEP have been integrated and intervened in the realization of the project (80). A second objective is to assess the experience lived by the PwMS participating in the CANSEP trial and their perceptions related to the use of THC and CBD as a clinical intervention.

The limitations of the CANSEP trial may be related to data collection through patient-reported outcome measurements which could inaccurately estimate problems and not be suitable for all patients (82). However, a daily diary developed to monitor medication adherence and scheduled phone calls between visits will ensure proper data collection. Also, the variability in understanding the definition of spasticity among patients could be a limitation in the assessment of this symptom although we provide the same description to all participants.

## Knowledge transfer

4

At the end of the study, we will conduct a robust knowledge transfer. We plan a variety of strategies (e.g., health cards and video clips) in collaboration with patient partners to train PwMS interested in using cannabinoids-based medicines in an appropriate level of literacy. For clinicians, we will create a tool of shared decision-making. To translate results to the health care level, we will build on our involvement in national/international research, clinical and training organizations. For the general population, we plan to organize public conferences to raise awareness of societal issues as well as participation in events organized yearly by the CHUM.

## Conclusion

5

CANSEP will provide a better characterization of CBD and THC’s influence on spasticity and on immune and pharmacological factors which could directly influence spasticity treatments and guide both health professionals and PwMS in the decision-making care process.

## Ethics statement

The CANSEP study involving humans was approved by the Research Ethics Board of Centre de recherche du Centre hospitalier de l’Université de Montréal, on September 9, 2022 (approval #21.303). The study was conducted in accordance with the local legislation, institutional requirements and the Declaration of Helsinki. The participants provided their written informed consent to participate in this study.
